4. Assess the costs of the specialist rehabilitation intervention, and of the ongoing care assistant support, and calculate relative cost-effectiveness, including consideration of savings from service use offsets;

5. Investigate the acceptability of the new service delivery models (specialist domiciliary rehabilitation with and without ongoing support from trained care assistants) from the perspectives of all stakeholders including commissioners, MDT members, care assistants, service managers, patients and family carers;

6. Deliver guidance for commissioners, providers and policy makers about the acceptability, clinical and cost-effectiveness of different models of specialist neurological rehabilitation.

The **hypotheses **are that:

1. A package of domiciliary multidisciplinary specialist rehabilitation will benefit:

a. People with Parkinson's in terms of maintaining mobility and independence (primary outcome for patients), and improving wellbeing and health-related quality of life,

b. Family carers in terms of reduced strain (primary outcome for carers), and improved health-related quality of life, and

c. Society through reduced use of other health and social care services, including hospitalisations and admissions to long term care.

2. The addition of four months of ongoing support from trained care assistants will help to maintain the benefits of the specialist team rehabilitation, and avoid the fading of effects that typically accompanies the withdrawal of input.

3. The intervention will be acceptable to major stakeholders, and that barriers and facilitators to wider implementation will be identified.

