### Sample size calculations

Patient sample size calculations were based on detecting clinically meaningful differences in the primary patient outcome measure. Carer sample sizes reflect the findings of our previous work that suggest that 79% of people with Parkinson's have a carer [10].

We will recruit 270 people with Parkinson's over a 12 month period across the three areas, 90 of whom will be randomly allocated to each of the three groups. This calculation is based on the numbers of people with Parkinson's needed to detect differences between groups in patient primary outcome measure score.

Assuming a similar level of variation in Self Assessment Parkinson's Disease Disability Scale [46] to the day hospital trial [11], in order to detect a difference in the disability score of 1.25 (assuming SD = 2.5, size = 5%, power = 80% and a 2 sided test), 64 subjects with Parkinson's disease are needed in each of the three groups.

Assuming a similar level of variation in Carer Strain Index [56] to the day hospital trial [11], in order to detect a difference in the Carer Strain Index of 0.535 (assuming SD = 1.07, size = 5%, power = 80% and a 2 sided test), 64 carers are needed in each of the three groups. In the previous study, 79% of community dwelling people with Parkinson's had a live-in carer [10]. Thus, if we have 64 carers per group, this will necessitate 246 [(64*3)/0.79 = 243.04] Parkinson's subjects, i.e 82 per group.

In the previous day hospital trial the loss to follow-up/non completion/missing data rate between recruitment and six month assessments was 26%. However, in this trial, participants attended the day hospital for treatment (six visits) and research assessments (four visits), and difficulties with transport and inter-current illness accounted for missing data and drop-out. We expect less attrition in the SPIRiTT trial because participants will receive both treatment and the research assessments in their own homes, at times convenient to them.

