The economic analysis will evaluate the costs of the intervention in relation to all patient and carer consequences/outcomes [64]. In addition, a cost-effectiveness analysis will be conducted, using standard techniques of economic appraisal [65]. Mean differences between groups (Group A (specialist rehabilitation only) vs. group C (normal care controls); Group B (rehabilitation with ongoing support) vs. Group A) in the primary outcome measures (disability score for patients, carer strain) and in QALYs (patients only) adjusted for baseline values in an analysis of covariance, will be used to measure effectiveness. If statistically significant differences between groups are found, incremental cost-effectiveness ratios will be calculated to show the extra cost incurred per unit of therapeutic gain/QALY gain. Secondary cost-effectiveness analyses will be conducted using other outcomes as measures of effectiveness.

The impact of uncertainties in the estimation of costs and outcome variables will be explored using one way and probabilistic sensitivity analysis. Bootstrap methods will be used to represent uncertainty of estimates, either for constructing confidence intervals or probability curves. Sensitivity analysis will also investigate the cost-effectiveness of the interventions for people with different levels of disability at baseline.

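### Cost-effectiveness ratios depend on a significant effect, so the plan can withhold a result it promises and, when it reports one, favours overestimated effects

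*Protocol article*

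**What the plan says.** The Economic evaluation section takes adjusted mean differences in disability, carer strain and QALYs as its effect measures: "in QALYs (patients only) adjusted for baseline values in an analysis of covariance, will be used to measure effectiveness". The contrasts listed are A versus C and "Group B (rehabilitation with ongoing support) vs. Group A) in the primary outcome measures". The next sentence sets the rule: "If statistically significant differences between groups are found, incremental cost-effectiveness ratios will be calculated". Nothing elsewhere in the article lifts it.

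Three other statements bear on it:

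- Objective 4, in the Background, is to "calculate relative cost-effectiveness, including consideration of savings from service use offsets", with no condition on the effect. Objective 6 promises commissioners guidance on cost-effectiveness.
- The Economic evaluation section opens with an evaluation of costs against all patient and carer outcomes. This also carries no condition.
- Its last paragraph plans probabilistic sensitivity analysis and says "Bootstrap methods will be used to represent uncertainty of estimates, either for constructing confidence intervals or probability curves".

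**The concern.** A decision about value needs the joint distribution of incremental cost and incremental effect. A significance test looks at the effect alone, against zero, and ignores cost. The plan itself expects that savings in other services may offset the cost of the interventions. An arm could therefore be good value through such savings with an effect that misses p < 0.05, and the rule would then report no ratio for it.

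The rule also selects. An estimate that must exceed 1.96 standard errors to be used is, on average, larger than the truth. It then becomes the denominator of the cost per unit of gain, so the ratio tends to look too favourable.

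Finally, the rule covers QALYs, although the sample size is set only on disability and carer strain. At stake is whether, and how fairly, the ratio behind Objectives 4 and 6 is reported.

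**Working it through.** **Inputs (Sample size calculations).** Patients: "difference in the disability score of 1.25 (assuming SD = 2.5, size = 5%, power = 80% and a 2 sided test", giving "64 subjects with Parkinson's disease are needed in each of the three groups". Carers: "Carer Strain Index of 0.535 (assuming SD = 1.07, size = 5%, power = 80% and a 2 sided test), 64 carers are needed". Both are a standardised effect of 1.25/2.5 = 0.535/1.07 = 0.5.

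**The plan's figure reproduces.** The normal approximation 2(1.96 + 0.84)²/0.5² gives 63. The exact two-sample t-test gives 63.77, rounded up to 64, with power 80.1%. For recruitment, (64 × 3)/0.79 = 243.04, and 243.04/0.90 is about 270, or 90 per group. After 10% loss, 81 patients per group remain. For carers, 90 × 0.79 × 0.90 is about 64 per group. I therefore use n = 81 and n = 64.

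**Chance of no ratio, and inflation when there is one.** In SD units, SE = √(2/n) and λ = d/SE. With P the probability of significance:

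- P = 1 − Φ(1.96 − λ) + Φ(−1.96 − λ)
- chance of no ratio = 1 − P
- inflation = [λ + (φ(1.96 − λ) − φ(1.96 + λ))/P]/λ

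Example, n = 81 and d = 0.5: SE = 0.157, λ = 3.18, P = 0.889, φ(1.96 − λ) = 0.189. No ratio: 11%. Inflation: (3.18 + 0.189/0.889)/3.18 = 1.07.

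Per contrast, without covariate adjustment:

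| True effect | No ratio, n = 81 | Inflation, n = 81 | No ratio, n = 64 | Inflation, n = 64 |
|---|---|---|---|---|
| 0.5 SD (design) | 11% | 1.07 | 19% | 1.12 |
| 0.4 SD (assumed) | 28% | 1.18 | 38% | 1.27 |
| 0.3 SD (assumed) | 52% | 1.43 | 60% | 1.57 |
| 0.25 SD (assumed) | 64% | 1.66 | 71% | 1.83 |

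**With the planned analysis of covariance.** SE is multiplied by √(1 − r²), where r is the correlation between baseline and follow-up. The document gives no r, so the values are assumptions, with the stated SD taken as that of the score. At n = 81 and d = 0.3:

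- r = 0.5: λ = 2.20, P = 0.60; no ratio in 40%, inflation 1.29
- r = 0.7: λ = 2.67, P = 0.76; no ratio in 24%, inflation 1.15

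At d = 0.5 and r = 0.7, the chance of no ratio falls to about 0.6%.

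**Both planned contrasts.** A versus C and B versus A share arm A. In simulation without adjustment, both are significant in 78% of trials (n = 81) or 62% (n = 64) if each true effect is 0.5 SD. If B versus A is only 0.25 SD, an assumption, the figures are 28% and 18%.

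**QALYs.** No SD, target difference or power is given, so no probability can be calculated.

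**The case against.** The strongest reply is that only a ratio is withheld. The comparison of costs with all consequences, the comparison of service costs between groups and the adjusted mean differences are all planned without condition. A reader might infer that the trial gives no cost-effectiveness answer when p > 0.05; the text does not support that. This part of the reply stands.

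A reader might also see an outright contradiction with the bootstrap paragraph. There is none. That paragraph is not expressly conditional, and uncertainty in cost and effect can be shown without a reported ratio. The article simply does not say whether the curves would be produced when the condition fails.

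The reply is also right that the only documented effect is 0.5 SD, where the loss and the inflation are modest. At n = 81 the average of true over estimated effect among significant results is then about 1.00, so the ratio itself is hardly biased. The condition could further be read as met by any one measure or contrast, and then a trial with no ratio at all would be rarer than the per-contrast figures suggest.

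On B versus C, the Statistical methods section plans that comparison for outcomes, and (A − C) + (B − A) recovers it within one model. Its absence from the cost-effectiveness contrasts is a secondary point.

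None of this justifies the condition. Covariate adjustment makes it bite less often but does not remove it.

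**Conclusion.** The concern holds in this limited form. The article states a positive rule that can withhold a ratio which Objective 4 sets as an aim without condition, and that selects overestimated effects when a ratio is given. This is not a detail left to a fuller document.

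At the design effect the size is modest. The larger figures rest on assumed effects below 0.5 SD, for which the document gives no support either way, and they shrink with adjustment. It would therefore be wrong to say that the ratio will usually be missing. For QALYs the risk is unknown. The primary clinical comparisons are not affected.

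**What to change.** Delete the significance condition. For disability, carer strain and QALYs, always report incremental cost, incremental effect, and the cost-effectiveness ratio or net benefit, with bootstrap uncertainty and acceptability curves, whatever the p-value. Present the three strategies together, including B versus C, so that any dominance of A can be seen. State that the bootstrap and probabilistic analyses do not depend on a significance test.

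The cost is a change of wording and minor extra analysis. No new data or participants are needed.

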**Methods:**

A pragmatic three parallel group randomised controlled trial involving people with Parkinson's Disease and live-in carers (family friends or paid carers), and comparing: management by a specialist multidisciplinary team for six weeks, according to a care plan agreed between the professionals and the patient and carer (Group A); multidisciplinary team management and additional support for four months from a trained care assistant (Group B); usual care, no coordinated team care planning or ongoing support (Group C). Follow up will be for six months to determine the impact and relative cost-effectiveness of the two interventions, compared to usual care. The primary outcomes are disability (patients) and strain (carers). Secondary outcomes include patient mobility, falls, speech, pain, self efficacy, health and social care use; carer general health; patient and carer social functioning, psychological wellbeing, health related quality of life. Semi structured interviews will be undertaken with providers (team members, care assistants), service commissioners, and patients and carers in groups A and B, to gain feedback about the acceptability of the interventions. A cost - effectiveness evaluation is embedded in the trial.

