## Design/Methods

### Design

A pragmatic three parallel group randomised controlled trial. People with Parkinson's in group A will be assessed and managed by a specialist MDT according to a care plan that is agreed amongst the professionals and with the patient and carer. Group B will additionally receive ongoing support for four months from a trained care assistant. Group C will receive normal care (no coordinated MDT care planning or ongoing support). Follow up will be for six months to determine the impact and relative cost-effectiveness of the two interventions. Qualitative interviews will be undertaken with providers (MDT members, care assistants), service commissioners, and patients and carers in groups A and B, to gain feedback about the acceptability of the interventions. The CONSORT diagram [42] summarises the design (Figure 1).

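### Incremental cost-effectiveness ratios are made conditional on a significant effect, which conflicts with the unconditional aim to calculate relative cost-effectiveness

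*Protocol article*

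**What the plan says.** The Economic evaluation section names the effect measures: mean differences in the two primary outcomes (patient disability, carer strain) "and in QALYs (patients only) adjusted for baseline values in an analysis of covariance, will be used to measure effectiveness". The contrasts are A vs C and B vs A. The next sentence sets the rule: "If statistically significant differences between groups are found, incremental cost-effectiveness ratios will be calculated". It does not say what happens when a difference is not significant.

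Elsewhere the economic aim carries no condition:
- Objective 4 (Background) is to assess the costs of the interventions and "calculate relative cost-effectiveness, including consideration of savings from service use offsets".
- The Abstract gives the purpose of follow-up as to "determine the impact and relative cost-effectiveness of the two interventions, compared to usual care", and the Design section repeats this.

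The Economic evaluation section also plans one-way and probabilistic sensitivity analysis, and adds: "Bootstrap methods will be used to represent uncertainty of estimates, either for constructing confidence intervals or probability curves".

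**The concern.** Whether an intervention is good value depends on the joint distribution of incremental cost and incremental effect. A significance test on the effect alone does not settle this in either direction. An arm that saves money through reduced service use, as hypothesis 1c expects, could be good value with a favourable effect that misses 5%. An arm with a clearly significant effect could be poor value. For example, an effect with z = 1.9 fails a two-sided 5% test although about 97% of a normal uncertainty distribution lies on the favourable side.

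Two things follow from the rule. Commissioners get no cost per unit of benefit or per QALY when the test is not significant, although the objectives promise relative cost-effectiveness. When the test is significant, the effect in the denominator has been selected for being large, so cost per unit of gain can look too low. The condition also sits badly with the bootstrap and probability curves planned in the same section, since these exist to show decision uncertainty whatever the p value.

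**Working it through.** **Inputs** (Sample size calculations section): disability difference 1.25, SD 2.5, two-sided 5%, power 80%, 64 required per group, 10% loss, 90 recruited per group. The carer figures (0.535, SD 1.07) give the same standardised effect: 1.25/2.5 = 0.535/1.07 = 0.5.

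**The plan's own figures.** The normal approximation gives n = 2(1.96 + 0.842)²/0.5² = 62.8, so 63 per group. The t-test version gives 63.8, so 64, as stated. Recruitment is 64 × 3/0.79 = 243.04, and 243.04/0.90 is about 270, or 90 per group. Both reproduce.

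**Set-up.** I take n = 64 (the design minimum) and n = 81 (90 less 10%). The standard error of a difference is SE = 2.5 × √(2/n), which is 0.442 at 64 and 0.393 at 81. The smallest estimate that meets the condition is 1.96 × SE, which is 0.87 and 0.77 points. With m = true difference/SE:
- P(significant) = Φ(m − 1.96) + Φ(−m − 1.96).
- Mean estimate given significant and favourable, divided by the truth = 1 + φ(1.96 − m)/[m Φ(m − 1.96)].

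| True difference | n per group | m | Significant | Ratio withheld | Mean significant estimate | Relative to truth |
|---|---|---|---|---|---|---|
| 1.25 (planning) | 64 | 2.83 | 81% | 19% | 1.40 | 1.12 |
| 1.25 (planning) | 81 | 3.18 | 89% | 11% | 1.33 | 1.07 |
| 0.625 (assumed) | 64 | 1.41 | 29% | 71% | 1.14 | 1.83 |
| 0.625 (assumed) | 81 | 1.59 | 36% | 64% | 1.04 | 1.66 |

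**Effect on the ratio.** With incremental cost held fixed, the ratio moves with true effect/estimated effect. At the planning effect, the mean of that quantity among significant favourable results is 0.995 (n = 81) or 0.945 (n = 64), so the average ratio is nearly unbiased or about 5% low. At half the planning effect, the ratio evaluated at the mean significant estimate is 1/1.66 = 0.60 or 1/1.83 = 0.55 of its true value.

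**Both contrasts.** By simulation, if each step (C to A, A to B) is worth the full 1.25 points, both contrasts meet the condition on disability in 62% (n = 64) or 78% (n = 81) of trials. If each step is worth 0.625, both do so in 3% or 6%.

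**Limits.** The standard errors are unadjusted. The section specifies analysis of covariance, which would reduce them by an amount the document does not give. If the baseline correlation were 0.6 (an assumption), SE would be multiplied by √(1 − 0.36) = 0.8. At half the planning effect and n = 81, power would then be 51% rather than 36%, and the exaggeration 1.39 rather than 1.66. The n = 81 figures are for patients only. About 71 carers per group are expected at recruitment, with 64 as the critical value, so the n = 64 rows are the closer guide for carer strain.

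**The case against.** The strongest reply is that the condition applies to one statistic, not to the economic evaluation. The same section sets costs against all patient and carer outcomes, says that a cost-effectiveness analysis will be done, and specifies the adjusted mean differences. Intervention costs and service-use costs are to be compared across groups so that offsets are visible. The bootstrap and sensitivity analyses carry no stated condition. This stands. A reader might infer that the whole cost-effectiveness answer is withheld after a non-significant result, but the text does not support that. What is lost is the ratio. It remains unclear whether the bootstrap sentence depends on a ratio having been calculated or stands alone.

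A reader might also infer that the condition screens the trial's long list of outcomes and picks which of them get a ratio. It follows a sentence naming three measures in two contrasts, which is six tests. The sentence on secondary cost-effectiveness analyses comes later and has no significance condition.

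It is tempting to add that QALYs are the measure most likely to miss significance. The document gives no QALY standard deviation or target difference, so their power cannot be computed.

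Finally, the large bias figures need a true effect well below plan, which the document does not give. That also stands, and the smaller effect is labelled here as an assumption. It is not far-fetched for B vs A, which isolates the added care-assistant support.

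None of these points defends the condition itself. It is explicit current text with no alternative branch, so a separate analysis plan could only replace it, not fill a gap.

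**Conclusion.** The concern holds for the incremental cost-effectiveness ratio. The significance condition is the wrong rule for a quantity that depends jointly on cost and effect, and it conflicts with the unconditional aim in the Abstract, objective 4 and the Design section.

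The size of the problem depends on the true effect. At the planning effect, a ratio on disability would be missing in roughly one trial in nine to one in five for a given contrast, and the selection bias in the ratio would be negligible to small. It would therefore be too general to say that the rule always makes cost per unit of gain look too low. At half the planning effect the ratio would be missing in about two-thirds of trials, and the bias would be substantial when it is reported. These figures rest on normality, an unadjusted standard error and, for the half-size effect, an assumption.

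Sample size, primary outcomes and data collection are unaffected, and nothing is lost if the rule is corrected before analysis. It should be fixed, but it does not threaten the trial's validity.

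**What to change.** Delete the significance condition. For every planned contrast and effect measure, report the incremental cost, the incremental effect and their joint bootstrap uncertainty whatever the p value, as a cost-effectiveness plane with an acceptability curve, or as net benefit with an interval. Give a ratio where it is interpretable, and state dominance where it is not. State also that the bootstrap and sensitivity analyses do not depend on a significant effect. The change does not require choosing a different lead effect measure.

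The cost is one amended sentence and a little extra reporting. No additional patients or data are needed, since the cost data and the bootstrap are already planned.

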### Risks and adverse events

An adverse event (AE) is any unfavourable or unintended sign, symptom, syndrome or illness that develops or worsens during the period of the trial. A serious adverse event (SAE) is any adverse event which is life threatening, or results in hospitalisation, disability or death. AE and SAE will be identified by research or intervention team members, or reported by participants. They will be recorded, assessed for seriousness, expectedness and causality by clinical members of the research team and monitored. Any SAE deemed to be directly related to, or suspected to be related to the intervention and unexpected will be reported to the study Steering Group and the Ethics Committee.

Risks to participants from the trial are considered small, and no higher than those of usual care. The aspects of the MDT intervention delivered by the individual therapists are standard practice and aim to improve self awareness and management. Home visits will include assessment of home safety and aids and adaptations required which may require in improvements in safety for participants. However, it is possible that encouragement to exercise more could result in falls that might not otherwise have occurred. The MDT members experienced professionals and will emphasise safety issues to participants. The care assistants will be fully trained, and will work under the instruction of team professionals, in the support of patients and carers and the implementation of the agreed care plan. Other potential harms to the experimental groups include depression if raised expectations are not met, distress when additional input is stopped, and loss of support from family and friends if the additional care is perceived to reduce the need for informal support.

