### Registration and randomisation

After consent and baseline data have been collected, eligible volunteers will be given a unique registration number by the project administrator and randomised to either: Group A - specialist rehabilitation, Group B - specialist rehabilitation and ongoing care assistant support, or Group C - usual care, control group. A separate randomisation sequence will be prepared by the study statistician prior to the commencement of the study for patients without live-in carers and for patients with live-in carers. In each instance, blocked randomisation will be used to formulate the sequence involving the three comparison groups. A non-computerised random number generator will create random permuted blocks of size three with an equal allocation ratio (with any of the six different group sequences being equally possible). The project administrator will inform: all participants of the group to which they have been randomised; the MDT of participants randomised to either of the treatment arms; the GPs of all participants about their involvement in the trial and the group to which they have been randomised. Since the project administrator will not be involved in the process of consenting volunteers into the study, and randomisation of eligible participants will be conducted in chronological order of study entry, no attempt will be made to conceal from the project administrator the next group to which the next patient would be allocated. However, only the project administrator and the study statistician will have access to each randomisation sequence.

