### Interventions

#### Specialist rehabilitation intervention (Groups A and B)

A multidisciplinary team comprising two each of PNS, physiotherapist, occupational therapist, and speech and language therapist will be assembled from local professionals. They will work one day per week for the trial, and in other duties for the rest of the time. Team members will visit the homes of participants to deliver a specialist rehabilitation package, tailored to individual needs. In order to make the outcome from the trial comparable to that of the previous study set in a day hospital [10-12], a similar programme of specialist rehabilitation will be provided comprising an initial assessment, and the formation of an agreed care plan reflecting the needs, wishes and expectations of the person with Parkinson's and carers. A group education component in the day hospital trial cannot be replicated in the domiciliary setting. As a substitute, the MDT will provide participants with a folder containing 13 fact sheets produced by Parkinson's UK and the research team, covering various aspects of living with Parkinson's including: medications, physiotherapy exercises, foot care, diet and nutrition, speech and language, relaxation techniques, sleep and fatigue, continence and bowel care, rights and benefits and advice for carers.

The rehabilitation intervention will be coordinated by the PNS, and will involve specialist input from each professional, over a period of six weeks. The team will meet face-to-face four times in each six week cycle to discuss patient plans and progress, and communicate by email and telephone at other times. Two hospital consultants (neurologist and geriatrician), both with a special interest in movement disorders, can be called upon by the MDT for medication changes or advice. Referrals to a range of other professionals will be made as required, including community psychologist, social care manager, continence adviser, dietician and pharmacist. Overall three days of professional time (including travel and meeting time) is allowed for each person with Parkinson's in the trial, but some people may need more and others less than this. This input is largely equivalent to the 9-12 hours of individualised nursing and therapy input, and flexible access to other professionals, in the previous day hospital trial.

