#### Ongoing support (Group B)

In addition to the programme of specialist MDT rehabilitation, participants randomised to Group B will receive ongoing support for four months from a care assistant trained in Parkinson's, starting at the end of the six week MDT intervention. The care assistants will be part of the MDT and will work under the supervision of the PNS. About one hour per week per patient is allowed for ongoing support, and contact will to be through a mix of home visits and telephone, through which the care assistant will monitor progress in implementation of the agreed care plan and report back to the MDT. If required, MDT members may continue to provide input. Care assistants will be recruited to the project from local health and social care employers and trained using the material developed by the research team [45], and through shadowing MDT members.

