#### Usual Care/Control (Group C)

Participants in the control group will continue to receive care as usual (no coordinated MDT care planning or ongoing support). When informed of their group allocation, they will be sent locally relevant and generic information about Parkinson's disease. This is a small enhancement on the service they are likely to be receiving. In order to measure the impact of the interventions, this information will also be given to the participants in Groups A and B. At the end of the trial, people in the control group will be offered an assessment by the MDT, with advice, and the fact sheets provided to groups A and B, but additional services cannot be guaranteed.

Cross contamination between groups will be minimal because patients will be individually recruited to the study, and receive treatments tailored to their specific needs. Moreover, the intervention and research assessments will take place in participants' homes which will be geographically dispersed over the catchment areas of three large district general hospitals.

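### Adverse events are captured more fully in Groups A and B than in usual care, so comparing recorded events by group would be tilted by detection

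*Protocol article*

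**What the plan says.** The section on risks and adverse events gives three routes by which events come to light: "AE and SAE will be identified by research or intervention team members, or reported by participants". The definition is broad: "An adverse event (AE) is any unfavourable or unintended sign, symptom, syndrome or illness that develops or worsens during the period of the trial". The same section gives a view on relative risk, "Risks to participants from the trial are considered small, and no higher than those of usual care", and then names possible harms of the intervention: falls from extra exercise, depression, distress when input stops, and loss of informal support.

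Other sections show whom each route reaches.

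- **Registration and randomisation:** the project administrator informs "the MDT of participants randomised to either of the treatment arms". The team is not told of Group C.
- **Specialist rehabilitation intervention (Groups A and B):** "Team members will visit the homes of participants to deliver a specialist rehabilitation package, tailored to individual needs", over six weeks, with three days of professional time allowed per patient, travel and meetings included.
- **Ongoing support (Group B):** "About one hour per week per patient is allowed for ongoing support", for four months after the six weeks. The care assistant monitors progress and reports back to the team.
- **Usual Care/Control (Group C):** no coordinated team care during follow-up. Contact with the team comes only afterwards: "At the end of the trial, people in the control group will be offered an assessment by the MDT".
- **Outcome measures:** a research nurse visits all three groups at home at weeks 6, 24 and 36.

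**The concern.** One of the three detection routes is absent in Group C, present for six weeks in Group A, and present for about 24 weeks in Group B. In a degenerative disease, a definition that counts any symptom that develops or worsens makes the count depend on how often someone is looking. Between weeks 6 and 24, Group C has 18 weeks with no scheduled trial contact, while Group B has about an hour of support each week.

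An excess of recorded events in A or B could therefore be detection alone. A true excess could equally be dismissed as detection. The B versus A contrast, which isolates the care assistant, is affected too. The trial is meant to guide commissioners, so a harms table by group that cannot be interpreted would be a real loss.

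**Working it through.** The protocol gives no figure for event rates or capture, so there is no stated result to reproduce. The direction follows from the text. The size needs assumptions.

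**Inputs from the protocol.** There are 90 patients per group, so 180 in A and B together against 90 in C. The last assessment is at week 36. The intervention route is open for weeks 1 to 6 in A and weeks 1 to 24 in B. Care-assistant time in B is about 17 to 18 hours (4 × 52/12 = 17.3 weeks, or 18 weeks if counted as weeks 7 to 24, at one hour a week).

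**Assumed inputs.** Let q be the share of true events captured by the routes open to everyone (nurse visits and participant report). Let r be the share of the remainder that intervention staff pick up. True rates are taken as equal.

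**Formula.** Capture in C is q. Capture in a treated group is q + (1 − q)r. The apparent ratio is 1 + (1 − q)r/q, which exceeds 1 whenever r > 0 and q < 1.

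| q | r | Capture, treated | Apparent ratio to C |
|---|---|---|---|
| 0.40 | 0.50 | 0.700 | 1.75 |
| 0.50 | 0.50 | 0.750 | 1.50 |
| 0.60 | 0.50 | 0.800 | 1.33 |
| 0.70 | 0.30 | 0.790 | 1.13 |
| 0.80 | 0.25 | 0.850 | 1.06 |
| 0.95 | 0.10 | 0.955 | 1.005 |

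**Gradient from C to A to B.** Suppose events are spread evenly over 36 weeks and staff pick up half of the otherwise missed events while in contact. Then r is 0.5 × 6/36 = 0.083 in A and 0.5 × 24/36 = 0.333 in B. At q = 0.60:

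- capture in A is 0.60 + 0.40 × 0.083 = 0.633, a ratio to C of 1.06;
- capture in B is 0.60 + 0.40 × 0.333 = 0.733, a ratio to C of 1.22;
- the ratio of B to A is 0.733/0.633 = 1.16.

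The same reasoning shows that 1.75 is an extreme value. It needs r = 0.5 over the whole follow-up. Group A could not reach that with evenly spread events (at most 6/36 = 0.17), and Group B would need 0.5/(24/36) = 75% pick-up while in contact.

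**What a naive comparison could show.** With an assumed true risk of 40% everywhere and q = r = 0.5, recorded risks are 30% in A and B against 20% in C. The chance of nominal p < 0.05 (180 against 90) is then about 41%. With q = 0.7 and r = 0.3 they are 31.6% against 28%, and the chance is about 8.5%.

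**After the fix.** Counting only the common route sets r = 0, and the expected ratio is 1.00 if q is the same in every group.

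**The case against.** The section describes safety surveillance: events are recorded, assessed and monitored, and related unexpected serious events are reported onward. For that purpose, using every available detector is right. The statistical methods section lists the outcomes to be compared, and adverse-event counts are not among them. Nothing says that sources are pooled in a group comparison. The sentence on risk relative to usual care is a prior judgement, and the hypotheses contain nothing on harms. Participants in every group can report events themselves. This is also a condensed article, so event-form detail may sit elsewhere.

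Most of this stands. A reader might infer that harms will be over-counted in the treated groups and that the trial therefore cannot check its statement on risk. The documents do not support that, for three reasons.

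- The extra events would be real ones, more fully captured in A and B and under-captured in C.
- No formal test of event counts is planned, so no stated analysis is invalidated.
- Several of the harms that matter most are measured alike in all groups. Falls, the Hospital Anxiety and Depression Scale and a depression screening item are in Table 1 at every visit. Falls are compared between groups at weeks 24 and 36, and psychological wellbeing at weeks 6, 24 and 36. The economic evaluation collects A&E and inpatient use by self-report in all groups, checked against local records where possible.

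The objection does not remove the stated rule, which gives A and B a detection route that C lacks. The article sets this out itself, so the point does not rest on missing detail. Any table of recorded events by group, even a descriptive one, would carry the tilt.

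**Conclusion.** The concern holds in a limited form. Under the rule as written, capture of adverse events is fuller in A and B than in C, and fuller in B than in A. The direction follows from who is visited and for how long. The size cannot be derived from the documents: the range of about 1.0 to 1.75 rests wholly on assumed capture rates, is negligible if the common routes catch nearly everything, and has an upper end that is hard to reach over the full follow-up. The effect falls mainly on milder events outside falls, depression and hospital use. It bears on how group counts may be read, not on the primary outcomes or on the duty to record every event. It is worth correcting because correction is cheap.

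**What to change.** 1. Have the research nurse ask every participant the same scripted adverse-event question, with the same recall period in all groups, at weeks 6, 24 and 36. Word it about events, not treatment, so that it does not invite disclosure of allocation.
2. Record the source of each event: research nurse, participant report at another time, or intervention staff.
3. Base the main between-group comparison of non-serious events on the scripted question.
4. Compare falls, psychological wellbeing and hospitalisations using the outcome and service-use data already collected in all groups.
5. Report deaths and other serious events from all sources for every randomised participant. Restricting these to the scripted question would lose deaths and events in people who withdraw or miss a visit.
6. Keep recording events found only by intervention staff for safety oversight, and report them separately.

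The cost is one item at visits already planned, one field on the event form, and fewer events in the main comparison. One assumption remains: that participants answer the nurse's question equally fully in each group. People used to discussing symptoms with the team may not, so some caution in reading the table should stay.
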